#### Qualitative outcomes

Interviews will be conducted with ten participants with aphasia in each arm of the trial at 4 months post-randomisation. These interviews will explore participants’ experience of taking part in the study and also what has helped participants in adjusting to living with stroke and aphasia. They will probe what participants have found useful in terms of emotional well-being, confidence, and thoughts about the future. The interviews will also explore participant experiences of services they have received in terms of their psychological well-being post stroke. Those who received peer befriending will also be asked about their experiences of the intervention, its perceived benefits, and any difficulties. The subset of participants interviewed from the PEER arm of the trial will be re-interviewed at 10 months about the longer term impact of the stroke and aphasia and their perceptions about the intervention.

A sub-sample of five significant others from each arm will be interviewed at 4 months to explore the impact of the stroke and aphasia on their life and family life and their perspectives of the care received. Those in the PEER arm will also be asked about the administration and impact of peer befriending. All interviewed participants will be selected purposively to capture a diversity of views. Key sampling criteria for participants with aphasia are severity of aphasia and whether the person lives alone. Secondary criteria are geographical area, gender, mobility, GHQ-12 score, and ethnicity. For significant others, sampling criteria include relationship to person with aphasia (partner/spouse or child/other), ethnicity, gender, and GHQ-28 scores.

All befrienders will be interviewed after they have completed two cycles of befriending (minimum two visits per cycle) to explore their experience of the study, including reflections on programme training and delivery, support received, any concerns or difficulties, and perceived benefits of peer befriending.

#### Economic evaluation

The European Quality of Life measures, 5 dimensions, 5 levels (EQ-5D-5L) [58] will be collected for participants with aphasia at baseline, 4 and 10 months post-randomisation, and the Stroke-adapted CSRI at 4 and 10 months post-randomisation.

### Sample size

We will recruit in total 60 participants with aphasia (30 in each arm of the study). Allowing for a ~ 15% lost to follow-up rate, at least 50 will complete the study. With 60 participants recruited, we will be able to estimate a 95% confidence interval for the recruitment rate to within approximately 25%. This sample size will be adequate to estimate important parameters needed to inform the design and the sample size of a full trial, such as the standard deviation, consent rates, event rates. This sample size also meets recommended sample sizes for feasibility studies [59].

Although this is a feasibility study, we would like to estimate exploratory differences between the PEER and USUAL arms. If we assume we retain 50 participants at follow-up, a two-sided test, *α* = 0.05, and independence of participants, we will have 80% power to detect an effect size of approximately 0.8. The standard deviation of the primary GHQ-12 outcome in a generic population of patients with stroke has been shown to be approximately 3.6—this was using the 0 0 1 1 scoring, with total scores ranging from 0 to 12 [60]. This effect size corresponds to an approximate mean difference of 3 points between groups. This sample size is sufficient for these exploratory comparisons; however, in a definitive trial, we would want to have higher power to detect a smaller effect size. This feasibility study will give us a standard deviation specific to the group that we would be interested in recruiting for a definitive trial, so would help to inform such a sample size calculation.

### Statistical methods: data analysis

#### Feasibility outcomes

As SUPERB is a feasibility trial, the feasibility outcomes are the most important/will take precedence. We will calculate proportion who are eligible of those screened (number eligible/number screened), proportion who are eligible at first screen (number eligible/number screened at first screen) and second screen (number eligible/number screened at second screen), rate of eligibility per month, proportion who consent of those eligible (number who consent/number eligible), rate of consent per month, and rate of recruitment (participants randomised) per month. The frequency and proportion of people consented who withdraw overall, by study arm, and by those who do before and after randomisation will be presented. This will specifically include describing those in the PEER arm who decline consent at the second stage. Appropriate 95% confidence intervals will be constructed for all of the above measures.

#### Descriptive statistics

Trial flow data will be reported as outlined by the CONSORT statement. We will use descriptive statistics to document what usual care consists of, based on data from the CSRI. The primary and secondary outcomes will be summarised using summary statistics, for the entire trial population and by trial arm, at each trial time point. The primary and main secondary outcome means and confidence intervals will be plotted over time. These summary statistics will help inform sample size estimation for the definitive trial.

#### Outcome measures’ analyses

Despite the feasibility nature of the trial, we will compare the PEER and USUAL groups. These will be considered strictly exploratory. For primary outcome analysis, the comparison will be between the PEER and USUAL groups. The GHQ-12 will be scored 0 0 1 1 and summed, resulting in a 0–12 score range. This overall total GHQ-12 score will be analysed using linear mixed models with the 4 and 10 months post-randomisation measures as dependent variables, with a random intercept for individuals, and time, the baseline GHQ-12 score, a dummy variable indicating treatment group, the minimisation stratification factors, and any baseline variables that were imbalanced or that predicted missingness as independent variables to improve the plausibility of the missing at random assumption. A treatment group by time interaction term will be included to allow for extracting comparisons at the 4- and 10-month post-randomisation time points. These models will account for missing data using the maximum likelihood algorithm.

In addition, if at least some peer befrienders see multiple participants (e.g. > 2), we will explore the possibility of calculating the GHQ-12 intra-class correlation coefficient (ICC) by fitting a linear mixed effects model using the data from the PEER group with the 4 and 10 months post-randomisation measures as dependent variables and a random intercept for befriender to calculate the within-peer, between-peer, and total variability for clusters of participants seen by the same peer befriender. This ICC will help inform a sample size calculation for a larger trial and provide estimates of a peer befriender ICC to publish in the literature. If the DISCS is used as the main primary outcome instead of GHQ-12, it will be analysed in a similar manner.

The significant other outcomes and the secondary and exploratory participant with aphasia outcomes will be analysed in a similar manner to the primary outcome, comparing the outcomes between the PEER and USUAL groups. The peer befriender outcomes will be compared between the baseline and post-befriending time points using a paired t-test.

All analyses will initially be conducted on an intention-to-treat basis. A second per protocol analysis will be done on the primary and secondary outcomes, excluding participants who are not in compliance with the protocol. Participants deemed not compliant will include those who did not consent at the second stage, completed less than six peer befriending sessions, were found to be ineligible after randomisation based on the inclusion/exclusion criteria, and participants in the usual care group who received peer befriending outside the study as reported to assessors or measured using the CSRI (in addition to their removal, we may explore analysing them in the peer group).

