#### Missing data

The amount and reasons for missing data will be summarised overall and by treatment group. Missing data will be accounted for where mixed models are applied under the missing at random assumption using the maximum likelihood algorithm. The baseline characteristics of those missing follow-up and those with complete follow-up will be summarised and variables affecting missingness will be examined using a logistic predictor of missingness model. This will be done by generating a binary variable for missingness for the primary outcome variable 10 months post-randomisation (we will explore the need to do this either separately or combined for the primary and secondary outcomes) and regressing this on baseline variables. Any variables found to be important predictors of missingness will be included in the primary and secondary outcome models. From a health economic perspective, where there is missing data, we will analyse the data on a complete case analysis basis and additionally use mean imputation for missing values. This will allow for a sensitivity analysis indicating whether missing values could be biasing the data.

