## Discussion

This exploratory (phase II) RCT will evaluate the feasibility of a phase III RCT on the clinical and cost-effectiveness of peer befriending for people with aphasia post-stroke. Effect sizes with 95% confidence intervals will be estimated to check that the likely effect is within a clinically relevant range as confirmation that it is worth planning a definitive trial. This information together with acceptability of the study data, safety of intervention, participant recruitment, and retention rates will help us determine whether the definitive RCT is feasible and whether modifications are needed to the intervention and/or the protocol. As multiple outcomes are considered in this study, including qualitative data, we have not set specific targets for the feasibility outcomes. According to the CONSORT 2010 extension statement for pilot and feasibility trials, even when such targets are set, they may be best viewed as guidelines rather than thresholds for progression [62]. As recommended in the CONSORT 2010 extension statement, we will consult with key stakeholders, including our TSC and user advisory group, when considering whether to progress to a definitive trial and potential amendments to the protocol. We will draw on the ADePT model (A process for Decision-making after Pilot and feasibility Trials) [63] to explore the best pathway forward from this feasibility study. The ADePT model provides a framework which enables (1) systematic identification and appraisal of problems and potential solutions/amendments, (2) increased transparency in the decision-making process, and (3) a process to make clear any tensions which may exist between explanatory and pragmatic choices (i.e. potential solutions which may work well within the trial, but less well in the real world).

This paper reports protocol version 5 (4 July 2018). Ethical approval for the SUPERB trial was obtained on 31 January 2017. Approvals from all sites to begin recruitment were completed by 6th April 2017. Recruitment, in terms of identification of potential participants, was completed on 31st August 2018, with the last participant consented to the study 9th October 2018.

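### The GHQ-12 model names only a random intercept, which in its usual form pools the 4- and 10-month variances; stating visit-specific variances would be a free, minor improvement

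*Protocol article*

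**What the plan says.** Under Outcome measures' analyses, the protocol article analyses the GHQ-12 total by "linear mixed models with the 4 and 10 months post-randomisation measures as dependent variables", "with a random intercept for individuals". The fixed effects are time, baseline GHQ-12, treatment group, the minimisation factors, and baseline variables that are imbalanced or predict missingness. It adds: "A treatment group by time interaction term will be included to allow for extracting comparisons at the 4- and 10-month post-randomisation time points". No residual structure and no standard-error method is given.

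On incomplete follow-up, the same section says "These models will account for missing data using the maximum likelihood algorithm", and the Missing data section says "Missing data will be accounted for where mixed models are applied under the missing at random assumption using the maximum likelihood algorithm".

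The group comparisons are qualified: "These will be considered strictly exploratory". The Discussion nevertheless gives the intervals a role in planning the next trial: "Effect sizes with 95% confidence intervals will be estimated to check that the likely effect is within a clinically relevant range".

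**The concern.** With two visits, a random intercept plus a single residual variance is compound symmetry: one total variance and one covariance. The treatment effect is free to differ by visit, but the variance behind each visit's standard error is an average over both. If the true variances differ, the more variable visit gets too narrow an interval and the less variable visit too wide a one.

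Unequal spread is plausible in this population. Participants are selected for low distress, the score runs from 0 to 12 with a floor at 0, and on such a scale the mean and the spread tend to move together.

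The missing-data approach also leans on the covariance. The 4-month score informs a missing 10-month score only through the model's implied regression of one on the other, and that slope is wrong if the variances are wrongly pooled.

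At stake are the visit-specific effects and 95% intervals that the Discussion takes into the judgement on a definitive trial.

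**Working it through.** **The plan's own figure first.** From Sample size: 50 retained (25 per arm), two-sided α = 0.05, effect size about 0.8, SD 3.6. Power is 80.7% by the normal approximation and 79.1% by the noncentral t, so the stated 80% reproduces. Also 0.8 × 3.6 = 2.88, about the 3 points stated, and 60 × 0.85 = 51, consistent with at least 50 retained. None of this depends on the covariance structure of the mixed model.

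**Assumption.** The article gives one SD (3.6, from a generic stroke population) and none by visit. Let r be the ratio of the larger to the smaller visit SD, taken over a range.

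**Closed form, one residual variance.** The fitted variance at each visit is about the mean of the two true variances. Hence:

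- SE ratio (model/true), less variable visit: √((1 + r²)/2)
- SE ratio, more variable visit: √((1 + r²)/(2r²))
- Coverage: 2Φ(1.96 × SE ratio) − 1

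| r | SE ratio, less variable | Coverage | SE ratio, more variable | Coverage |
|---|---|---|---|---|
| 1.0 | 1.000 | 95.0% | 1.000 | 95.0% |
| 1.1 | √1.105 = 1.051 | 96.1% | 1.051/1.1 = 0.956 | 93.9% |
| 1.2 | √1.22 = 1.105 | 97.0% | 1.105/1.2 = 0.920 | 92.9% |
| 1.25 | √1.28125 = 1.132 | 97.3% | 1.132/1.25 = 0.906 | 92.4% |
| 1.5 | √1.625 = 1.275 | 98.8% | 1.275/1.5 = 0.850 | 90.4% |

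**Simulation 1.** 25 per arm, complete data, SD 2.5 at 4 months and 2.5r at 10 months, within-person correlation 0.5, REML, 800 trials per cell. Coverage with the random intercept at the more and less variable visit was 93.1% and 97.4% at r = 1.25, and 90.6% and 98.5% at r = 1.5. Unstructured covariance gave 94.5% to 95.8%. At r = 1.0 both models gave about 94% to 95%.

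**Simulation 2.** 30 per arm, 7.5% missing at 4 months and 15% at 10 months (unrelated to outcome), correlation 0.5, REML, 800 trials per row. Coverage is shown as 4 months / 10 months:

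| SDs (4 / 10 months) | r | Random intercept | Unstructured |
|---|---|---|---|
| 3.6 / 3.6 | 1.0 | 94.8% / 96.4% | 95.3% / 95.6% |
| 3.0 / 3.6 | 1.2 | 96.8% / 92.9% | 95.5% / 95.1% |
| 2.5 / 3.6 | 1.44 | 98.0% / 89.3% | 94.8% / 93.0% |
| 1.8 / 3.6 | 2.0 | 99.8% / 86.4% | 94.8% / 94.8% |

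The Monte Carlo standard error is about √(0.95 × 0.05/800) = 0.8 points. At SDs 3.0/3.6 the mean model SEs were 0.888/0.917 under the random intercept and 0.806/0.999 under unstructured, against empirical SEs of 0.826/1.004. Both simulations used normal outcomes, so the floor of the score is not represented.

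**Dropout.** Suppose the correlation is 0.5 and 10 months is the more variable visit. The true slope of the 10-month on the 4-month score is 0.5r. Compound symmetry implies about 0.5 × 2r/(1 + r²). At r = 1.25 that is 0.625 against 0.488; at r = 1.5 it is 0.75 against 0.462. In the set-up of simulation 1, with dropout in the usual-care arm rising with the 4-month score, the 10-month contrast differed from the unstructured fit by about 0.09 points (r = 1.25) and 0.17 points (r = 1.5). Against the 3-point design difference that is 0.09/3 = 3% and 0.17/3 = 6%. The 10-month SE with 25 per arm is 3.125 × √(2/25) = 0.88 and 3.75 × √(2/25) = 1.06, so the shift is 0.10 and 0.16 of an SE.

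**The case against.** A reader might infer that the random intercept forces equal variances and that the reported intervals will therefore be wrong. The article does not support that. A random intercept only adds a constant component; equality comes from a constant residual variance, which the article does not state. A random intercept with visit-specific residual variances, or with robust standard errors, fits the same words. Such detail is commonly settled in an analysis plan or full protocol, and neither is shown. This part of the objection stands.

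Nor does the article show that the SDs differ. Selection is on the DISCS, not the GHQ-12. Hospital recruits often wait 6–8 weeks between recruitment and baseline. Baseline GHQ-12 is a covariate, not an outcome, so the selection argument bears more on baseline against follow-up than on 4 against 10 months. This stands too: the ratios above are assumptions.

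Finally, the consequence is limited. Feasibility outcomes take precedence, the comparisons are exploratory, and planning SDs come at least in part from the by-arm, by-visit summaries under Descriptive statistics, outside the model. The Discussion weighs the intervals alongside acceptability, safety, recruitment and retention, with no set targets.

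What the objection does not remove is that the article frees the mean by visit "to allow for extracting comparisons at the 4- and 10-month post-randomisation time points" but names a variance structure whose usual implementation does not, when a more general one is available at almost no cost.

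**Conclusion.** A minor point that holds conditionally. Fitted with one residual variance, the stated model gives both visit contrasts an averaged variance, and their intervals err in opposite directions if the true SDs differ. The closed form and both simulations agree on direction and size: negligible to small at SD ratios up to about 1.2, and material only at larger ratios, with coverage of about 90% at the more variable visit when the ratio is 1.5. Everything rests on the assumed ratio and on the default residual structure, so no error is demonstrated.

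A reader might also infer that dropout seriously biases the 10-month contrast. The figures do not bear that out: the shift is a few per cent of the design difference, and it requires dropout linked to the 4-month score in one arm as well as unequal variances.

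**What to change.** In Outcome measures' analyses, or in the analysis plan if the detail is kept there, state an unstructured 2×2 residual covariance for the 4- and 10-month scores. Alternatively, keep the random intercept and allow a separate residual variance at each visit. The two are equivalent when the covariance between visits is non-negative and no larger than the smaller variance; otherwise the unstructured form is the more general. Leave the fixed effects unchanged. Apply the same structure to the secondary, exploratory and significant-other outcomes, and to the DISCS if it becomes primary.

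The cost is one sentence and one extra covariance parameter, with no new data. If the variances are in fact equal, almost nothing is lost: at SDs 3.6/3.6 the mean model SEs were 0.972/1.001 with the unstructured form and 0.973/1.005 with the random intercept.

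### The primary mixed model admits baseline variables chosen for chance imbalance, without list or cap, and its small-sample interval method is left at maximum likelihood

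*Protocol article*

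**What the plan says.** Under Outcome measures' analyses, the protocol article sets out a linear mixed model for the 4- and 10-month GHQ-12 totals. It has a random intercept per person and terms for time, arm, arm by time, baseline GHQ-12 and the minimisation factors. The covariate list then ends with "any baseline variables that were imbalanced or that predicted missingness as independent variables to improve the plausibility of the missing at random assumption". On estimation it says: "These models will account for missing data using the maximum likelihood algorithm". The secondary, exploratory and significant-other outcomes are to be analysed in a similar manner.

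The Missing data section adds a logistic model for missingness of the 10-month primary outcome and states: "Any variables found to be important predictors of missingness will be included in the primary and secondary outcome models". It again names maximum likelihood under missing at random.

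On size, the Sample size section says "We will recruit in total 60 participants with aphasia (30 in each arm of the study"), with about 15% loss. Its power statement begins "If we assume we retain 50 participants at follow-up, a two-sided test, *α* = 0.05".

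The Discussion says that effect sizes with 95% confidence intervals will be used to check whether a definitive trial is worth planning.

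**The concern.** Two separate matters meet in this model.

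**Covariate rule.** After 1:1 randomisation, an observed baseline difference between arms is chance. It does not show that the variable predicts GHQ-12, nor that it predicts who is lost to follow-up. Adding it therefore does nothing for the missing-at-random assumption. With no list, threshold or cap, the model can be settled only once data are in hand. If the chosen variables are not prognostic, adjusting for them costs precision.

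**Estimation.** Full ML variance estimates take no account of the fixed effects fitted. With about 50 people and at least 10 fixed effects this matters, and more so as covariates are added. The article names ML and mentions no REML, t reference or small-sample correction.

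At stake is the honesty of the confidence interval used in judging whether to go on to a definitive trial.

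**Working it through.** **Inputs from the article.** 60 randomised 1:1, at least 50 followed up; minimisation on aphasia severity (3 levels), recruitment area (3 levels) and wheelchair use (2 levels) (Randomisation); model terms as above.

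**Assumptions not in the article.** Normal outcome; within-person correlation ρ = 0.3-0.7; number of added variables k = 0-8; imbalance threshold and number of candidate variables as stated below.

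**1. The plan's own figure.** The plan states: "we will have 80% power to detect an effect size of approximately 0.8". With 25 per arm, d = 0.8 and two-sided 0.05, power = Φ(0.8 × √12.5 − 1.96) = Φ(0.868) = 80.7%; the noncentral t gives 79.1%. With SD 3.6, 0.8 × 3.6 = 2.88, about 3 points. Both reproduce. The article states no coverage figure.

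**2. Parameter count.** Intercept, time, arm, arm by time, baseline score, and 2 + 2 + 1 dummies make 10 fixed effects. Eight of these act at person level (all but time and the interaction). The missingness screen rests on about 9-10 missing outcomes (15% of 60 = 9; 60 − 50 = 10).

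**3. How many variables chance imbalance would add.** With 25 per arm, the standardised difference of a continuous variable has SE √(2/25) = 0.283. Then P(|difference| > 0.25) = 0.377, so 10 candidates give 3.8 entries and 15 give 5.7. If imbalance means p < 0.05 or p < 0.10, 10-15 candidates give only 0.5-1.5.

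**4. Coverage under ML with z, one time point, 50 people with complete data.** With total variance 1, the person-mean part is v_b = ρ + (1−ρ)/2 and the within-person part is v_w = (1−ρ)/2. ML shrinks them on average by (n−p)/n and (n−2)/n, where p = 8 + k. The expected ratio of estimated to true variance of the effect is

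R = v_b(n−p)/n + v_w(n−2)/n.

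For ρ = 0.5, k = 0: R = 0.75 × 42/50 + 0.25 × 48/50 = 0.63 + 0.24 = 0.87. Coverage is about 2Φ(1.96√0.87) − 1 = 93.2%, or 92.8% once sampling error in the variances is included. On the latter basis:

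| Added variables k | Coverage, ρ = 0.3 to 0.7 |
|---|---|
| 0 | 93.1% to 92.6% |
| 2 | 92.7% to 91.9% |
| 4 | 92.2% to 91.3% |
| 6 | 91.7% to 90.6% |
| 8 | 91.2% to 89.8% |

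**5. Simulation of the mixed model.**

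| Setting | ML with z | REML with t |
|---|---|---|
| n = 50 complete, ρ = 0.5, k = 0, 2, 4, 6 | 91.9, 92.3, 91.9, 91.0% | 94.3-95.5% |
| Same, variables with \|difference\| > 0.25 chosen from 10-15 (3.8-5.7 enter) | 90.8-91.0% | 94.9-95.6% |
| Same, chosen at p < 0.05 or p < 0.10 (0.5-1.5 enter) | 92.0-92.8% | 94.7-95.3% |
| 60 randomised, 50 at 10 months, ρ = 0.5 or 0.7, k = 0-6 | 90.1-93.4% | 93.5-95.5% |
| 60 randomised, about 16% lost, ρ = 0.6, 0, 12 or 20 candidates (0, 4.4, 7.3 enter) | 92.7, 91.7, 89.9% | about 95% |
| 60 randomised, 50 at 10 months, ρ = 0.5, none, then 2.7-6.6 chance-imbalanced variables | 93.3%, then 91.1-91.7% | 94-95% |

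Monte Carlo SE is about 0.4 points in the first three rows (4,000 runs) and about 0.7 in the fourth and fifth (1,500 runs).

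**6. Precision.** When non-prognostic variables enter through imbalance, the true SD of the estimate rises from 0.26 to 0.27-0.30 in one simulation (4-15%) and from 0.29 to 0.31-0.33 in another (7-14%).

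**7. Source of the shortfall.** The same selected covariates under REML with t give about 95%. The under-coverage therefore comes mainly from ML, the z reference and the parameter count, not from selecting on imbalance as such.

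**The case against.** The strongest reply is that maximum likelihood is named as the way missing data are handled. It need not exclude REML, and the degrees-of-freedom method and imbalance threshold are details that a statistical analysis plan or the full protocol may settle. This stands, and it is why the coverage figures are conditional. A reader might infer that the plan's intervals cover 90-92%. The text does not fix that: it would take full ML, z-based intervals and several added variables together.

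A reader might also infer that the SD and ICC carried into the definitive trial are understated. The article does not support this. Under Descriptive statistics, the summary statistics are what inform that sample size, and ML does not bias them. The befriender ICC comes from a separate model in the PEER arm alone, for which no bias has been worked out here.

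Other points have partial force:
- The missing-at-random clause can be read as attached only to predictors of missingness, whose inclusion is standard. On that reading the imbalance criterion has no stated purpose at all.
- Adjusting for a variable that happens to be prognostic can gain precision. Imbalance does not identify such variables.
- The Blinding section gives statisticians A/B codes until the main primary analysis is done. This limits choosing covariates to favour an arm, but does not fix the model.
- The comparison is strictly exploratory, and feasibility outcomes take precedence.

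**Conclusion.** The imbalance criterion is wrong as written. It is a stated rule, so a threshold supplied elsewhere would limit its effect but not justify it. Its cost is an open model and, where the added variables are not prognostic, an SD of the estimate roughly 5-15% higher.

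The estimation point is conditional. Under plain ML with z, coverage is about 92-93% with the pre-set covariates and about 90-92% with roughly 3-8 more, against about 94-95% for REML with t. This rests on a normal outcome and a within-person correlation of 0.3-0.7.

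The consequence is moderate. The feasibility outcomes are untouched, and the effect-size interval is only one of several inputs to the go-ahead judgement described in the Discussion.

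**What to change.** Under Outcome measures' analyses:
- Delete imbalance as a ground for entering a covariate.
- Fix the covariates as the baseline outcome plus the three minimisation factors. Name in advance at most one or two missingness covariates; aphasia severity is already in the model. Align the Missing data section with this.
- State that the models are fitted by REML, which is valid under the same missing-at-random assumption, with Kenward-Roger or Satterthwaite degrees of freedom.
- Apply the same wording to the secondary, exploratory and significant-other models.

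The cost is a change of wording and a software option. The downside is slightly wider intervals.
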